#### 3.3.1. Degree of DFU Healing

Wound healing is defined as the complete epithelization of the wound and is assessed through the RESVECH 2.0-PT [41], a useful and validated tool to monitor the progression of chronic wounds of any etiology through six main parameters: wound area, depth and involved tissues, wound margins, type of tissue in the wound bed, levels of exudates, and presence of signs of infection/inflammations. This questionnaire will be filled out by the participant’s physician or nurse at the end of consultations to monitor DFU progression. Scores range from 0 to 35, where zero indicates complete healing and 35 corresponds to the worse possible wound.

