### 2.4. Randomization

All eligible patients will be randomly assigned to one of the four groups—TG1, TG2, ACG, or PCG—in varying size blocks so that, over time, all groups can have a similar number of participants [36,37]. An independent researcher (Researcher 4), unaware of the numeric coding for each group, will create the randomization sequence using an online random number generator (https://www.graphpad.com/quickcalcs/randomize1/, accessed on 15 December 2021) with a 1:1 allocation, using random block sizes of 12. Researchers 2, 3, and 4 are blind to the block size used in the randomization procedure.

A priori stratification was defined considering the three hospitals where data collection will take place, as well as two common comorbid conditions deemed as factors of poor prognostic outcomes in patients with DFUs, specifically chronic kidney disease (CKD) and peripheral arterial disease (PAD) [38,39], to ensure that distribution of patients between groups is balanced in terms of confounders. Thus, randomization is stratified according to (i) hospitals; (ii) CKD and its disease stages (without CKD/CKD stage 1 and 2/CKD stage 3 and 4); and (iii) PAD (without PAD/with PAD), in a total of 12 possible strata.

Participants’ blinding will be maintained throughout the conduct of the trial, whereas Researchers 1, 2, and 3 will be aware of the allocation since they are responsible and will conduct the TG1 and ACG sessions. Quantitative data analysts will be blinded to participant allocation. The randomization process will be conducted at the end of each week to reduce the time interval between the randomization and the beginning of interventions.

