#### 3.2.2. Clinical Information

Clinical data will be collected through the Clinical Questionnaire, developed specifically for this study, to be completed by the patients’ physician or nurse in the three assessment moments. This questionnaire asks about the type and duration of diabetes, complications associated with diabetes, diabetic foot type, DFU location and duration, concomitant treatment, ulcer healing time, and new DFUs. The clinical questionnaire also includes the Perfusion, Extent, Depth, Infection, and Sensation (PEDIS) classification system, proposed by the International Working Group of the Diabetic Foot, thus gathering information regarding the five most important categories to evaluate the DFU stage and progression [40].

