### 3.3. Measures of Primary Outcomes

Primary outcomes are DFU healing, physiological indicators of healing prognosis, DFU impact on QoL, and physical and mental QoL.

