### 4.2. Adherence to the Treatment Plan

Patients will be fully informed about the study goals, procedures, and potential benefits that may arise from the results of the DFU treatment. Assessment moments, intervention, and placebo sessions will be scheduled for diabetic foot appointment days so that patients will not have to go to the hospital on purpose to participate in the study. Before the appointment day, Researchers 1, 2, and 3 will call patients to remind them of their appointment with the research team for the purpose of the study. Participants will be asked to complete the last assessment (T2) even if they miss the mid-term assessment (T1).

To engage the health professional staff (e.g., physicians, nurses, podologists), meetings will be held with the physicians responsible for the multidisciplinary consultation of diabetic foot and head nurses (in the three hospitals involved in the study), in order to introduce the study and clarify any questions that may arise.

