## 7. Discussions

Given the huge challenge of distress in patients with DFUs, and the limited data evaluating the healing process and QoL of patients with chronic DFUs, the study of the efficacy of two economic stress reduction interventions in clinically distressed patients with chronic DFUs is proposed.

This paper describes the PSY-DFU study protocol, the first national and international multicenter study to address the contribution of psychological variables in DFU healing and QoL. The study also tests the effects of two psychological interventions: individual relaxation and hypnosis, both with guided imagery, on wound healing, physiological indicators of wound healing prognosis, and QoL.

Many complicating factors of diabetes compromise the healing process, making effective treatments challenging. The compliance rate in the treatment groups is one of the major difficulties experienced so far. This is, in part, due to the fact that patients with chronic DFUs often present a long history of medical care, and yet many fail to adhere to the medical treatment and self-management, thus developing negative expectations about psychological interventions. Moreover, in the treatment groups, when DFU is completed healed, the intervention ends, which also contributes to the low-rate compliance. Regarding the DFU progress monitoring, this study would benefit from more advanced and accurate techniques to assess wounds, such as imaging devices. However, none of the three participating hospitals have yet adopted imaging systems to routinely measure DFUs. In addition to the limited strategies to improve adherence to treatments, and the use of more traditional tools to measure chronic DFUs, the non-fully blinded design also represents a limitation of this research.

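### The wound score behind the first-named primary outcome is completed by treating clinic staff whom no stated blinding step covers, which leaves the DFU-healing comparison with the passive control group open to rater bias

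*Protocol article*

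**What the plan says.** **Outcome and rater.** Section 3.3 states: "Primary outcomes are DFU healing, physiological indicators of healing prognosis, DFU impact on QoL, and physical and mental QoL". Section 3.3.1 measures DFU healing with RESVECH 2.0-PT, built from six parameters: area, depth and tissues involved, margins, wound-bed tissue, exudate, and signs of infection or inflammation. "Scores range from 0 to 35, where zero indicates complete healing". The form is completed by the patient's "physician or nurse at the end of consultations to monitor DFU progression". Section 3.2.2 gives the clinical questionnaire, which includes PEDIS and ulcer healing time, to the patient's "physician or nurse in the three assessment moments".

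**Blinding.** Section 2.2 labels the trial participant-blinded. Section 2.4 says of participants that their "blinding will be maintained throughout the conduct of the trial", that Researchers 1, 2 and 3 know the allocation because they run TG1 and ACG sessions, and that "Quantitative data analysts will be blinded to participant allocation". Treating physicians and nurses are not mentioned.

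**Contact between clinic and sessions.** Section 4.1.1 places treatment sessions in a hospital consulting room. Section 4.2 schedules assessments, treatment sessions and placebo sessions on foot-clinic days, and adds that "meetings will be held with the physicians responsible for the multidisciplinary consultation of diabetic foot and head nurses" to present the study. Section 4.1.2 gives the PCG standard care only. Section 7 notes that "in the treatment groups, when DFU is completed healed, the intervention ends", and lists incomplete blinding and the absence of imaging devices among the limitations.

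**The concern.** Four of the six RESVECH parameters (margins, wound-bed tissue, exudate, signs of infection) call for clinical judgement, and no imaging check is available at the three hospitals. If the person scoring knows that a patient is attending study sessions, a slightly kinder score is possible without any intent to mislead. Blinding the analysts does not help, because the bias is already in the data they receive.

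The exposed contrast is an important one: Section 5.1 bases the sample size on the difference between treatment and passive control. A leniency that follows session attendance would appear there as a treatment effect. Wording that allows either a physician or a nurse, with no rule on continuity, also permits a different rater at T0, T1 and T2 in the same patient.

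**Working it through.** **1. Who could know what.** Setting the sections side by side:

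| Group | Sessions | Run by | Distinguishable by attendance? |
|---|---|---|---|
| TG1 | four, every two weeks, about 45 min | Researchers 1–3 | from PCG only |
| TG2 | same schedule | external hypnotherapists | from PCG only |
| ACG | same schedule | Researchers 1–3 | from PCG only |
| PCG | none | – | yes, from the other three |

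Seeing a patient go to sessions separates the PCG from the rest. It does not separate treatment from active control. Patients could still describe the content of their sessions during the consultation, so the ACG contrast is better protected but not immune.

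**2. The plan's own figure.** Inputs from Section 5.1: difference 1.93, SD 6, power 80%, significance level 5% (two-sided in Section 5.2).

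n = 2 × (1.960 + 0.842)² × 6² / 1.93² ≈ 152

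The figure 152 reproduces, as the number per arm of a two-group comparison. The plan uses it as the total for four groups, which is 152 / 4 = 38 per arm, and 152 × 1.11 ≈ 169, or 42 per arm, after the dropout allowance. That use of 152 is a separate matter. Here it only fixes the arm sizes the trial plans, 38 and 42.

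**3. Effect of a rating shift when there is no true effect.** Assumptions: 1.93 and SD 6 are on the RESVECH scale (Section 5.1 does not name the scale), and leniency b is 0.5 to 1.0 point (the documents give no value). A leniency of 0.5 is 0.5 / 1.93 = 26% of the planned difference, and 1.0 is 1.0 / 1.93 = 52%.

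SE = 6 × √(2/n), and the two-sided rejection probability is 1 − Φ(1.96 − b/SE) + Φ(−1.96 − b/SE).

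| n per arm | SE | b = 0.5 | b = 1.0 |
|---|---|---|---|
| 38 | 1.38 | 6.5% | 11.2% |
| 42 | 1.31 | 6.7% | 11.9% |

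The nominal rate is 5%. A shift of 0.25 point would give 5.4% at either arm size, so a very small leniency does little harm.

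**The case against.** The strongest reply is that silence is not unblinding. Nobody who delivers sessions completes RESVECH, so rating is already separated from delivery. Nothing says clinic staff are told the arm: the meetings in Section 4.2 introduce the study, and stopping sessions at healing requires only that word of healing reaches the session team, not that the arm reaches the clinic. Researchers 1 to 3 interview patients in every arm, so contact with the research team alone identifies no one. RESVECH is described as validated, area and depth are more measurable than the other items, and full epithelization (score 0) leaves less room for leniency than mid-scale scores. Section 7 also concedes incomplete blinding.

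Most of this stands, and it limits the point to what raters can learn. It does not remove it. The article lists who is and is not blinded and also names the rater, so the gap lies between two stated design elements and is not a detail lost in condensing. The concession in Section 7 is general and names no wound raters.

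The arithmetic is a plain two-group test, whereas Section 5.2 plans repeated-measures models with baseline DFU stage as a control variable. Such adjustment would not remove a shift in post-baseline scores. If it lowered the residual SD, the same shift would be more likely to reach significance.

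Three stronger readings are tempting, and the documents do not support them:

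- **Raters are unblinded, or will change between visits.** The text permits both and states neither.
- **Changing raters add noise beyond the plan.** The pilot SD of 6 may already contain rater error, so no loss of power can be claimed.
- **False-positive rates of 11 to 31%.** These arise for the same shifts at 152 per arm, a size the trial does not plan.

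**Conclusion.** The point holds in a limited form. As written, the raters of the first-named primary outcome fall under no blinding step and can learn who attends sessions, so the DFU-healing comparison with the PCG is open to rater bias. The ACG comparison is less exposed.

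The size is illustrative. With a leniency of 0.5 to 1.0 point, the false-positive rate would be about 6.5 to 11% at 38 per arm, or 6.7 to 12% at 42, in place of 5%. This rests on two assumptions that the documents cannot confirm: the scale of 1.93 and SD 6, and the size of the leniency. Because the repair is cheap, the change should be made.

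**What to change.** Add to Sections 2.4 and 3.3.1:

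- Staff who complete RESVECH are not told the arm and do not arrange sessions.
- RESVECH is completed before any contact with the session team that day.
- The same rater scores T0, T1 and T2 in a given patient where possible.
- The rater records at each assessment whether the arm was known.

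Report rater awareness by arm, and treat the ACG contrast as the one better protected from rater bias when healing results are interpreted. Do not use an analysis restricted to ratings made unaware of the arm. Awareness arises after randomisation and would probably differ between the PCG and the session arms, so such a restriction would break the randomised comparison.

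The cost is a short instruction to clinic staff and one extra item on the form, with no additional staff. Masking will remain imperfect, because patients may reveal their arm in the consultation. That is why awareness should be recorded.

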#### 3.3.2. Physiological Indicators of Healing Prognosis

Physiological indicators include a biochemical parameter (HbA1c), inflammatory (IL-6, TNF-α, lymphocyte populations) and angiogenic (VEGF) markers, miRNAs (miRNA-21, miRNA-155), and immune cells (lymphocytes T effective and naïve). The quantification of HbA1c in the plasma will be performed using the competitive inhibition enzyme immunoassay Cloud Clone Corp. The quantification of the plasma inflammatory cytokines levels (IL-6) and tumor necrosis factor (TNF-α) will be performed using a LEGENDplex™ Human Angiogenesis Panel 1 Mix and Match (9-plex). Blood lymphocyte populations will be assessed in the whole blood by flow cytometry and an automated hematological cell counter. Levels of VEGF will be assessed through the serum by ELISA from Cell Signaling Technology. miRNA-21 and miRNA-155 will be assessed through blood collected in a tube from Qiagen (PAXgene Blood RNA Tubes, Qiagen, Hombrechtikon, Switzerland), and subsequently, the RNA will be converted into cDNA by “miScript Reverse Transcription Kit” (Qiagen). Amplification of miR-21 will be done through the light Cycler system with SYBR Green PCR Kit. The control gene will be the RNU6B. Immune cells will be calculated through the ratio of lymphocyte effectors CD4/CD8 to lymphocyte naïve CD4/CD8 cells. Blood samples will be collected and processed in the clinical laboratory of two of the three hospitals where data collection will take place.

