Previous literature has emphasized the impact of stress on wound healing, almost exclusively in acute wounds, e.g., [12]. In fact, stress raises the level of cortisol, which has a negative impact on the immune system, particularly on wound repair due to immunity suppression [13,14]. By increasing the release of proinflammatory cytokines during tissue repair and driving tissue oxygen levels lower, psychological stress delays wound healing [15,16].

Stress may also impact the expression and function of microRNAs (miRNAs), important regulatory molecules that can be used as biomarkers for diagnosis or progression of complications from diabetes due to their ability to fine-tune cellular responses [17]. Thus, by modulating miRNA biogenesis, expression, and complex activity, stress can cause important changes in metabolism that may hamper DFU healing [18].

Glycemic control is one of the main strategies to monitor diabetes, reducing the complication of diabetes and the risk of hypoglycemia. Hemoglobin A1c (HbA1c) testing represents the best method to monitor glycemia in patients with diabetes, as it reflects levels of blood glucose over several weeks. Although distress has been associated with poor glycemic outcomes [19], the role of HbA1c in wound healing is not consensual. In fact, if some studies show direct associations between HbA1c levels and wound-healing rate, e.g., [20], other studies found no association between this biomarker and wound outcomes, e.g., [21].

Since there is evidence that psychological distress affects negatively wound healing [11], it is expected that reducing-stress interventions have positive implications on DFU recovery. Adjuvant interventions as relaxation training techniques have shown promising results in patients with diabetes [22,23] and patients with chronic DFUs [24,25]. Previous research also indicated hypnosis as an effective adjunct treatment in the management of diabetes, contributing to reduced blood glucose levels, better metabolic control, and increased blood flow to extremities, decreasing the risk of diabetic foot problems [26,27,28,29].

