## 5. Statistical Analysis

### 5.1. Sample Size

Using Sakpal’s formula [49] and according to the descriptive results of the pilot study [50], considering the difference in the mean (1.93) and standard deviation (6) of the treatment versus passive control groups, with a statistical power of 80% and a statistical significance level of 5%, a definitive RCT will require 152 participants. Considering a dropout rate for intervention sessions of 11%, a definitive RCT with four groups will require a sample size of 169 participants, with 42 patients per group [49].

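### HbA1c, one component of the physiological-indicator primary outcome, is specified as a plasma measurement, which is not a valid measure of the several-week glycaemia it is chosen to reflect

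*Protocol article*

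**What the plan says.** Section 3.3 of the protocol article sets the primary outcomes: "Primary outcomes are DFU healing, physiological indicators of healing prognosis, DFU impact on QoL, and physical and mental QoL". Section 3.3.2 lists the physiological indicators, and HbA1c is the single item under the biochemical label. The same section fixes specimen and assay: "The quantification of HbA1c in the plasma will be performed using the competitive inhibition enzyme immunoassay Cloud Clone Corp".

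The Background explains why HbA1c is measured: "Hemoglobin A1c (HbA1c) testing represents the best method to monitor glycemia in patients with diabetes, as it reflects levels of blood glucose over several weeks". Section 3.1 and Table 1 schedule the blood sample at T0, T1 and T2.

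Section 3.3.2 names other specimens for other assays. For lymphocytes: "Blood lymphocyte populations will be assessed in the whole blood by flow cytometry". For the angiogenic marker: "Levels of VEGF will be assessed through the serum by ELISA".

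**The concern.** Specimen and analyte do not match. Red cells carry the HbA1c, and preparing plasma removes them. Haemoglobin still found in plasma was released by lysis, in the body or while the sample was drawn and processed. HbA1c reflects glycaemia because it is the glycated share of the haemoglobin in circulating red cells. A quantity measured in the cell-free fraction, with no stated denominator, does not carry that meaning.

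At stake is the interpretation of one primary-domain measure. If the text is followed, a null result could reflect noise from sample handling, and a difference between groups could not safely be read as a change in glycaemic control. Analysis cannot repair this afterwards, because the cells have been separated off.

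**Working it through.** The protocol states no figure on this point, so there is none to reproduce. The check compares the passages and then adds one illustration.

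**Passages side by side**

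1. Purpose (Background): HbA1c is used because "as it reflects levels of blood glucose over several weeks".
2. Specimen (3.3.2): plasma.
3. Could plasma be a loose word for blood? The same section assigns whole blood to the lymphocyte counts, serum to VEGF and a dedicated RNA tube to the miRNAs. The authors distinguish specimens, so the natural reading is that plasma is meant.
4. Does another section correct it? No. Sections 3.1 and 3.2.2 and Table 1 mention neither whole blood nor lysate for HbA1c, and none gives a reporting unit or a total-haemoglobin denominator.
5. Status (3.3 with 3.3.2): HbA1c belongs to the second of four primary domains. That domain also holds IL-6, TNF-α, lymphocyte populations, VEGF, two miRNAs and a T-cell ratio.

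**Illustration (all CVs are assumptions; none is in the documents)**

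Suppose the plasma result is a concentration equal to free haemoglobin multiplied by its glycated fraction, with the two independent and log-normal. The share of log-variance due to glycaemia is then

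share = s_g² / (s_g² + s_h²), where s² = ln(1 + CV²),

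with g the glycated fraction and h the free haemoglobin.

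Worked case, CV_g = 20% and CV_h = 50%: s_g² = ln(1.04) = 0.0392; s_h² = ln(1.25) = 0.2231; share = 0.0392 / 0.2623 = 14.9%.

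| CV of free haemoglobin | CV_g 15% | CV_g 20% | CV_g 25% |
|---|---|---|---|
| 10% | 69.1% | 79.8% | 85.9% |
| 20% | 36.2% | 50.0% | 60.7% |
| 30% | 20.5% | 31.3% | 41.3% |
| 50% | 9.1% | 14.9% | 21.4% |
| 100% | 3.1% | 5.4% | 8.0% |

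Under this model glycaemia dominates only when free haemoglobin is nearly constant between samples, and the article states nothing that would secure this. If the result were divided by total haemoglobin in the same sample, the free-haemoglobin term would cancel and some glycaemic signal would remain. The article states no such step.

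**The case against.** The strongest reply is that this is a wording slip. The next sentence of 3.3.2 concerns plasma cytokines, and the section is loosely drafted elsewhere. A journal article may also leave sample preparation, lysis and normalisation to the full protocol or a laboratory procedure, so their absence here does not show that they are not done. That is fair, and the point does not rest on missing detail. It rests on the specimen the article does state, which is wrong for the stated purpose. If it is a slip, it still needs correcting.

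A reader might infer more, namely that the assay would follow haemolysis and carry no glycaemic information. The documents do not support so absolute a reading. The article gives neither the unit nor the preparation, the kit procedure is not available, and the illustration runs from 3% to 86% depending on the assumed variation. The supportable statement is that the reading depends heavily on leaked haemoglobin and is not a valid HbA1c.

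Nor does the fault invalidate the primary outcomes as a whole. It touches one marker in one domain, and the Background itself says that the role of HbA1c in wound healing is disputed. Stratifying randomisation by kidney disease (2.4) also limits any imbalance between arms in factors such as anaemia. It does not turn plasma into the right specimen.

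**Conclusion.** The point holds within these limits. As written, 3.3.2 specifies a specimen that does not fit the analyte or the purpose given in the Background, and following it would give an invalid measurement for one component of the physiological-indicator primary outcome. Ulcer healing, both quality-of-life instruments and the other markers are unaffected.

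The conclusion needs only two facts: HbA1c sits in red cells, and plasma is cell-free. It does not depend on the illustration, whose CVs are assumed and shown only as a range. The documents do not allow the actual error to be sized, and they do not show whether plasma has in fact been assayed.

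**What to change.** In 3.3.2, change the HbA1c specimen from plasma to whole blood (haemolysate), using the blood already drawn at T0, T1 and T2, and state that HbA1c is reported as a percentage of total haemoglobin or in mmol/mol. The hospital laboratory's routine HbA1c method is preferable. If the full protocol or laboratory procedure already specifies this, correct the article to match.

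If plasma was in fact assayed for participants already enrolled, do not report or interpret those values as HbA1c or as glycaemic control.

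The cost is small. Blood is taken at all three visits, and 3.3.2 already uses whole blood for flow cytometry. There are two downsides:

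- Routine methods may differ between laboratories, and 3.3.2 has samples processed at two of the three hospitals. Randomisation is stratified by hospital, which limits the effect on group comparisons.
- The Discussion describes difficulties met so far, so the trial appears to be under way and earlier samples may not be re-assayable.

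Medical records should not be assumed to fill such gaps. Section 6 covers consent to record access, but nothing shows that HbA1c is recorded at each assessment, and the description of the clinical questionnaire in 3.2.2 does not list it.
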